## AIM

To conduct a prospective multicentre randomised study comparing total mortality, cancer-specific mortality, recurrence-free survival, economic cost effectiveness, and quality of life (QOL) in patients having two different schedules for follow-up after radical resection for colorectal cancer.

## BACKGROUND

The value of follow-up programmes after radical surgery for colorectal cancer has been a controversial issue for many years, and the scientific evidence supporting it remains sparse. Many cohort and case-control studies have supported the effectiveness of follow-up (Rosen *et al.*, 1998) (Figure 1 – lower case), but, until recently, randomised controlled trials have reported only ambiguous findings regarding the efficacy of follow-up on mortality (Kievit & Bruinvels, 1995). Nonetheless, despite the sparse evidence, follow-up programmes are being used in most clinics treating colorectal cancer patients (Mella *et al.*, 1997).

The reasons for follow-up include:

- to obtain a better overall survival.
- for scientific purposes
- for psychological reasons

There is no doubt that the outcome of follow-up programmes can be considered from both efficacy and cost perspectives (Kievit, 2002).

Recently, two systematic reviews with meta-analyses have been published investigating the same five randomised controlled trials (Renehan *et al.*, 2002; Jeffery *et al.*, 2002). The conclusions of these reviews were the same: more intensive follow-up leads to lower mortality than sporadic or less intensive follow-up. Subsequently, another randomised study was published confirming this conclusion (Secco *et al.*, 2002). We have conducted a meta-analysis of all the randomised trials, as shown in Figure 1 (upper case). We found a highly significant effect of more intensive follow-up compared with less intensive follow-up (Peto Odds Ratio=0.62, 95% confidence interval:0.51-0.76,  $P < 0.001$ ).

However, these meta-analyses do create problems, mainly due to the heterogeneity in both the intense and less intense follow-up regimens. The individual trials used different control modalities and, in fact, the intensity of control in one study could be considered more aggressive than the “intensive” group in other studies. The quality of the trials has also been questioned, as a high (and probably not generalisable) number of local recurrences was seen in the two studies which showed the highest effect of intensive follow-up (Secco *et al.*, 2002; Pietra *et al.*, 1998). The results of these meta-analyses should, thus, be viewed with caution.

Further, the meta-analyses are not able to identify either which follow-up modality to use, or the intensity (*i.e.*, investigation intervals) of the follow-up. Although some authors claim that we know enough to make evidence-based recommendations (Smith & Bear, 1998) this claim is clearly arguable – a point of view that is supported by the debate that followed Renehan’s paper in *British Medical Journal* in April 2002 (see [www.bmj.com/cgi/eletters/324/7341/813#23550](http://www.bmj.com/cgi/eletters/324/7341/813#23550))

Nonetheless, the published studies do imply that finding extraluminal recurrences (local recurrence after rectal cancer and liver metastases after colorectal cancer) mainly causes the obtainable benefit. The search for intraluminal recurrence does not alter the mortality. As the incidence of local recurrence after rectal cancer is rapidly declining due to better surgical techniques and the use of adjuvant treatment, the effect of looking for local recurrence after rectal cancer might be limited. A subgroup analysis of three studies looking for liver metastases shows an effect on

survival in one of the meta-analyses (Figure 2) (Jeffery *et al.*, 2002). Moreover, the preoperative work-up for occult liver metastases was not routine when the referred trials were conducted.

In conclusion, the effectiveness of high-volume follow-up programmes after radical surgery for colorectal cancer on overall survival is still not sufficiently elucidated to create evidence-based guidelines. Despite this the Current Oncological Practice (COP) is moving towards high intensity follow-up programmes (Figueredo *et al* 2003, Worthington *et al* 2004, Anthony *et al* 2004). A Minimal acceptable practice (MAP) might be just as good. It, thus, seems justified to perform a randomised controlled trial randomising patients to high- or low-volume control programmes.

## **Most used methods for control**

### *Luminal recurrence:*

Endoscopy is the chosen method, but luminal recurrence is seldom and programmes looking for luminal recurrence show no effect (Renehan *et al.*, 2002)

### *Local recurrence after rectal cancer:*

Endorectal ultrasound (US) has a high sensitivity and specificity (Löhnert *et al.*, 2000), especially when combined with guided biopsy (Hünerbein *et al.*, 2001). MR-imaging (MRI) is perhaps even more sensitive, but expensive (Pegios *et al.*, 2002).

### *Liver metastases:*

Average sensitivity for US is 55%, for CT 72%, MDCT 96% (Acta Rad. vol 46, no 1, feb. 2005, 9-15), for MRI 76%, and for PET 90%. Of these, PET and MRI are not generally available.

### *General recurrence:*

PET is probably the most sensitive of detecting dissiminated disease Monitoring of carcinoembryonic antigen (CEA) remains controversial (Lennon *et al.*, 1994), but might be justified, if related to perioperative measurements (Renehan *et al.*, 2002; Li Destri *et al.*, 1998).

## **STUDY PROCEDURES**

### *Recruitment and Eligibility*

Centres will be recruited from all over Scandinavia, the UK, Poland, Hungary, Uruguay and Holland. At each participating centre, consecutive patients receiving radical surgery for colorectal cancer (emergency or elective) will be considered for inclusion. Those who are ineligible or who refuse consent will be followed in an observational follow-up design.

### Inclusion criteria:

- Radical elective or emergency surgery (R0-resection) for colorectal adenocarcinoma – with or without adjuvant treatment, and
- Age  $\leq$  75 years, and
- Provision of written informed consent for participation, and
- “Clean colon” verified by perioperative barium enema or colonoscopy last 3 months post-surgery, and
- Tumour stage:II-III ( $T_{any} N_{1-2} M_0$ ,  $T_{3-4} N_{any} M_0$ , Dukes’ B - C) as staged at the pretreatment staging procedure (clinical staging)

Pre- or postoperative chemotherapy and/or radiation therapy is allowed.

### Exclusion criteria:

- A clinical diagnosis of HNPCC (non hereditary polyposis colorectal cancer) or FAP (familial polyposis coli),
- Local resection for colorectal cancer (e.g., TEM-procedure),
- Life-expectancy less than 2 years due to concurrent disease (e.g., cardiac disease, terminal multiple sclerosis, liver cirrhosis),
- Inability to provide informed consent or refusal to do so,
- Inability to comply with the control or intense follow-up programme,
- Participation in other clinical trials interfering with the control-programmes
- Other or previous malignancies (except for non-melanoma skin cancer)

Informed consent (written) is obtained within 30 days after the primary tumour classification has been obtained. Patients refusing to participate should be asked for consent to be followed in the cohort, using data on their actual control-programme and their clinical course.

### **Randomisation and treatments**

Randomisation will take place by Internet from a central randomisation unit (appendix 12) placed at Department of Clinical Epidemiology in Århus Denmark. Randomisation will be stratified according to tumour stage and clinical centre. Randomisation will be blocked in variable groups of which the size will be kept secret for the participating centres. The allocation procedure should be concealed to the deliverers of treatment.

### **Study Follow-up Regimens**

CEA will (if possible) be measured on all colorectal cancer patients before surgery or preoperative adjuvant therapy, and one month after the completion of primary treatment. All patients should have “clean colon” within 3 months perioperatively, and at least one imaging procedure (Ultrasound, MRI, or CT) of the liver and X-ray of the lungs perioperatively. In both groups, an unlimited number of endoscopies are allowed. Interval diagnostic evaluation will be allowed for all subjects presenting symptoms.

A clinical visit 4-6 weeks after operation is recommended for information and allocation.

#### *1: Low frequency follow-up regimen*

- CEA preoperatively and one month postoperatively – a missing preoperative CEA is not considered an exclusion criteria, and will be handled as missing data.
- CEA, multislice CT/ or MRI of the liver and X-ray/CT of the lungs 12 and 36 month after surgery. Patients are instructed to contact their reference centre if symptoms of recurrence occur.
- If recurrent disease is suspected, a standardised work-up for diagnosis and treatment will be applied (appendix 2-3)

#### *2: High frequency follow-up regimen*

- CEA preoperatively and one month postoperatively – a missing preoperative CEA is not considered an exclusion criteria, and will be handled as missing data.
- CEA, multislice hepatic CT, or MRI and X-ray or CT of the lungs at 6, 12, 18, 24, and 36 months. Patients are instructed to contact their reference centre if they experience any symptoms of recurrence.

- If recurrent disease is suspected, a standardised work-up for diagnosis and treatment will be applied (appendix 2-3)

Patients with newly elevated CEA in whom recurrence cannot be found at other investigations could be sent for PET-scanning (if available). If this does not disclose metastatic disease, it should be repeated after 3 months (if the CEA is still elevated). For algorithm see appendix 2.

At each follow-up visit, a blood sample is taken for storage (-80°) for possible later analyses for prognostic or diagnostic factors.

In both groups, an unlimited number of endoscopies are allowed, but should be performed after the same schedule in each randomisation-group two groups. The same goes for CT/MRI/US of the pelvis for recurrence after rectal cancer. The local programmes in this respect should be registered centrally, and divergations from this programme should be registered in the CRF. Interval control should be performed in case of symptoms, and the procedures used should be according to the guidelines in appendix 2. These interval controls should be registered on the CRF. It is allowed to call patients for extra clinical follow-up after 48 and 60 months, as long as the programme is even in the two randomisation arms.

#### *Quality of examinations*

Before entering a trial, the individual centre should prove the high quality of their control-examinations. The central steering group's diagnostic board should approve five consecutive examples. Guidelines for examinations are listed in Appendix 1.

### **Patient treatment if recurrence**

If recurrence is suspected or verified, the patient-case should be evaluated in a local (country- or county separated) MDT conference, in order to decide and offer the best available treatment for the patient (salvage surgery, palliative chemotherapy and/or radiotherapy, no treatment). These groups also form the local steering-groups for the study. They should preferably include a surgeon, a radiologist, and an oncologist.

An algorithm for treatment of recurrence is found in Appendix 3.

### **Efficacy parametres**

The primary effect-parameter of the study will be total mortality and cancer-specific mortality after 5 years; the secondary endpoint will be time to diagnosis of recurrence (*i.e.*, recurrence-free survival).

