## **Statistical analysis and power**

Results will be evaluated both on an intention-to-treat basis and on an as-treated (per protocol) basis. Patients who withdraw their informed consent and, thus, change their control-programme remain in their allocation group when evaluated on the intention-to-treat basis, and are excluded when evaluated on the fulfilled protocol basis. Non-randomised patients and patients withdrawing their informed consent will be analysed separately.

On the basis of the results listed in Figure 1, an estimate of 5 years' mortality at 60% and a MIREDF (Minimal Relevant Difference) of 6% seem justified. With a risk of type 1 error at 5% and type 2 error of 15%, about 1,100 patients should be randomised to each group. With an expected dropout rate of about 20%, the planned number of randomised patients should be 2,500.

Survival data will be analysed according to the Kaplan-Meier method and comparison between groups will be performed with the log-rank method. Binominal data will be analysed with Chi-square statistics and continuous data with Mann-Whitney U test.

No interim analyses are planned, as this would stop inclusion for several years.

Level of significance two-sided  $p < 0.05$ .

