### Regarding **Efficacy parameters**:

As evidence suggested that the 3 year effect-parameter of total mortality and cancer-specific mortality to be an excellent surrogate to 5 years, the steering decided in September 2012 to publish both 3 and 5 years total mortality and cancer-specific mortality, along with the secondary endpoint of recurrence-free survival.

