### *Statistical analysis and power*

The primary effect parameter of the study will be total mortality and cancer-specific mortality after 5 years; the secondary endpoint will be time to diagnosis of recurrence (*i.e.*, recurrence-free survival) and quality of life.

Results will be evaluated both on an intention-to-treat basis and on an as-treated (per protocol) basis. Patients who withdraw their informed consent and thus change their follow-up programme will remain in their allocation group in evaluations conducted on an intention-to-treat basis, and will be excluded in evaluations conducted on a per-protocol basis.

Non-randomised patients and patients who withdraw their informed consent will be analysed separately.

On the basis of the results listed in Figure 1 in the protocol, an estimate of 5 years' mortality at 60% and a MIREDF (Minimal Relevant Difference) of 6% seem justified. With a risk of type 1 error at 5% and type 2 error of 15%, about 1,100 patients should be randomised to each group. With an expected dropout rate of about 20%, the planned number of randomised patients should be 2,500. Survival data will be analysed according to the Kaplan-Meier method. Comparisons between groups will be made using the log-rank method. Binominal data will be analysed with Chi-square statistics and continuous data will be analysed with the Mann-Whitney U test.

Level of significance = 5%.

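### Two unranked primary endpoints and two unranked analysis sets share one 5% level with no decision rule; if either 5-year ITT result may count, the false-positive risk is about 6.5–8%, not 5%

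*Combined protocol and SAP*

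**What the plan says.** - **Endpoints.** Protocol, Efficacy parametres: "The primary effect-parameter of the study will be total mortality and cancer-specific mortality after 5 years". Trial SAP, Statistical analysis and power: "The primary effect parameter of the study will be total mortality and cancer-specific mortality after 5 years". Each calls this a single parameter but lists two outcomes, and neither ranks them.
- **Analysis sets.** Protocol, Statistical analysis and power: "Results will be evaluated both on an intention-to-treat basis and on an as-treated (per protocol) basis". The trial SAP says the same. Neither set is named as the one that decides the trial.
- **Time points.** The amendment on efficacy parameters records a steering-group decision of September 2012 "to publish both 3 and 5 years total mortality and cancer-specific mortality". The word used is publish. The amendment does not call the 3-year results primary and gives them no test level.
- **Error rate.** The protocol's sample size starts "With a risk of type 1 error at 5% and type 2 error of 15" per cent, and the section closes with "Level of significance two-sided" at p < 0.05. The trial SAP also gives one 5% level. No interim analyses are planned.
- **Sample size.** Both documents take one 5-year mortality of 60% and one minimal relevant difference of 6 points, and arrive at about 1,100 per group.

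Nowhere is there an order of testing, a split of the 5%, or a statement of whether one or both endpoints must be significant.

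**The concern.** A 5% type 1 error describes one test, or a family of tests tied together by a rule. Here two endpoints share the primary label, each is evaluated in two sets, and no rule links them. If significance on either endpoint may be called a positive trial, the stated 5% is not held.

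The lack of a rule also matters apart from the error rate. If total and cancer-specific mortality disagree, or the ITT and per-protocol results disagree, the plan does not say what the trial concludes. The choice would then be made with the results in view.

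**Working it through.** **1. The plan's own figure.** With two-sided α = 5% and power 85%, (1.960 + 1.036)² = 8.98. For the log-rank test (Schoenfeld), events = 4 × 8.98 / (ln HR)², where HR = ln(1 − p₂)/ln(1 − p₁), and N per group = events / (2 × mean mortality).

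| 5-year mortality | HR | Events | N per group | Power at 1,100 per group |
|---|---|---|---|---|
| 63% vs 57% | 0.849 | 1,338 | 1,115 | 84.5% |
| 60% vs 66% | 1.177 | 1,348 | 1,070 | 86.0% |
| 60% vs 54% | 0.847 | 1,312 | 1,151 | 83.4% |

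The stated 1,100 is reproduced by the first two readings and is close under the third. In each case the 5% is spent once, on one mortality comparison.

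**2. Upper bounds.** If the tests were independent, the chance of at least one false positive would be 1 − 0.95ᵏ: 9.75% for k = 2, 18.5% for k = 4 and 33.7% for k = 8. The real tests share events, so the true figures are lower.

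**3. Allowing for correlation.** Under no effect, two log-rank statistics where one uses a fraction f of the other's events have correlation of about √f. The documents give none of the fractions, so these are assumptions:
- cancer deaths as a share of all deaths: 50–90% (correlation 0.71–0.95);
- share of 5-year deaths occurring by year 3: 60–70%;
- share of patients kept in the per-protocol set: 80–98%, with exclusion at random. The 95% and 98% cases were run only with the 70% share by year 3.

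Two million multivariate-normal draws per setting, each test at two-sided 5%, gave:

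| Results that could each count as success | Tests | Chance of at least one p < 0.05 | Multiple of 5% |
|---|---|---|---|
| Two endpoints, 5 years, ITT | 2 | 6.5–8.3% | 1.3–1.7 |
| Two endpoints, 5 years, ITT and per protocol | 4 | 7.3–11.6% | 1.5–2.3 |
| Two endpoints, 3 and 5 years, ITT | 4 | 9.7–13.0% | 1.9–2.6 |
| Two endpoints, 3 and 5 years, both sets | 8 | 10.8–17.8% | 2.2–3.6 |

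For the first row, a cancer share of 50% gives 8.3%, 70% gives 7.6% and 90% gives 6.5%.

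**4. Cross-check.** Log-rank tests on 4,000 simulated null trials per setting (2,500 patients, 60% mortality, 10% or 20% excluded per protocol) gave 6.3–8.8% for the two 5-year ITT tests, 9.5–12.7% for the four ITT tests and 12.2–16.6% for all eight. The simulation error near 8% is √(0.08 × 0.92 / 4,000) = 0.4 points, so the two methods agree.

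**5. Other rules.**
- *Both endpoints must be significant:* under no effect the chance cannot exceed 5%.
- *Split at 2.5% each:* the two 5-year ITT tests together run at 3.3–4.3%. Log-rank power at 1,100 per group falls to 75–79% across the three readings in step 1. Keeping 85% for 60% vs 54% needs 1,570 events, or 1,570 / (2 × 0.57) ≈ 1,380 per group before dropout.

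**The case against.** The strongest reply is that the plan fixes the primary time point at 5 years and nowhere says that a 3-year or per-protocol result could decide the trial. The amendment only promises publication. On that view the family is the two 5-year ITT tests, the excess is modest, and a reading that requires both endpoints would remove it. Most of this stands. It is why the 6.5–8% figure comes first and the larger ones are conditional. It does not supply the missing rule: the both-must-succeed reading is not written down, and neither is the primacy of ITT.

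A reader might go further than the documents allow in four ways.
- *That the real false-positive rate is two to three times 5%.* This needs a rule that any one of several results wins, together with event shares and exclusion rates that the documents do not give. For the two named primaries in one set, the multiple is 1.3–1.7.
- *That the 10-year analysis adds a further look.* It has its own SAP, is titled a post-trial analysis, and leaves out the patients from Uruguay. It does not belong in this family.
- *That the sample size was set for total mortality.* The text says only 5-year mortality. What can be said is that it was set for one mortality comparison.
- *That cause-of-death attribution, or the timing of salvage treatment, biases some of these results.* The documents do not say who assigns cause of death in the trial, and they give nothing that bears on the salvage argument. Neither is part of this point.

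**Conclusion.** The point holds as a missing decision rule with a moderate numerical consequence. The plan states a 5% type 1 error but leaves two primary endpoints and two analysis sets unranked. If either 5-year endpoint may count in the ITT set, the error is about 6.5–8%, given that 50–90% of deaths are from cancer. The ranges of about 10–13% (adding the 3-year results) and about 11–18% (adding per-protocol versions as well) apply only if those results could each be claimed as success, which the documents do not say. They also rest on the assumed 60–70% of 5-year deaths by year 3 and 80–98% of patients kept per protocol. Random exclusion is assumed throughout; selective exclusion could add bias that these figures do not cover. That the rule is missing is plain from the text, whereas the exact size of the inflation depends on these assumptions.

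**What to change.** State in the SAP:
1. The single primary analysis is the ITT comparison of 5-year total mortality, reported as a risk difference with 95% confidence interval and read against the plan's own 6-point difference.
2. Cancer-specific mortality at 5 years (ITT) is tested at 5% only if the first test is significant. This fixed sequence holds the two tests together at 5%.
3. The 3-year and per-protocol results are supportive, given with confidence intervals and no separate claim of significance.

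The cost is wording: no added patients, and no loss of power for the first test. The downside is that cancer-specific mortality cannot be claimed alone when total mortality is not significant. Splitting the 5%, or requiring both endpoints, would also close the gap. The split costs the power shown in step 5 of the working, and requiring both cannot give more power than the weaker of the two tests alone.

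The order has to be fixed before outcome data are seen. The 10-year SAP already describes the trial's findings, so a ranking of the 5-year results written at that stage or later must be reported as post hoc.

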### **Data collection**

In order to track all potentially eligible patients, a system for reporting all patients diagnosed with colorectal adenocarcinoma in the pathological departments of participating hospitals should be in place at each participating centre. All patients having radical surgery and who fulfil the inclusion criteria are to be reported to the secretariat. The reason for not including individual patients is to be reported. Case-record forms (CRF) (Appendix 6) for individual patients are to be filled in at the individual centres. Reports should be collected centrally after every planned or non-planned control. All registrations (CRF) are communicated centrally by means of an internet-based database with the central server placed at The Department of Clinical Epidemiology in Århus, Denmark after each visit (appendix 12).

Patients refusing to participate should be followed according to the individual departments' local guidelines. Each control-visit among patients in this group should be reported, if consent for observational follow-up is obtained.

If economically possible, each centre will receive a monitoring visit at least once a year.

The following data will be obtained on all randomised subjects and those who give consent for observational study:

- Baseline demographic, clinical, and lifestyle factors (date of birth, major chronic illnesses, smoking, alcohol intake, medications, etc);
- Results of all diagnostic evaluations for metastatic disease during the initial evaluation;
- Description of initial surgical, adjuvant, and radiation treatment;
- Postoperative final staging
- Findings from all cancer surveillance tests obtained after diagnosis;
- Detailed description of all cancer treatment applied after randomisation;
- Quality of life (QOL) assessment by telephone interview at 1, 3, and 5 years after randomisation. A standardised and evaluated QOL-instrument that takes follow-up regimens into consideration will be used. (See Appendix 3.)

